### Recruitment

2.5

For intervention development, a list of eligible and interested schools and colleges shall be prepared. The students, parents and teachers from these schools and colleges shall be requested to express their interest in participating in the FGDs and IDIs. The participants for the FGDs and IDIs shall be selected sequentially using a computer generated randomization process. The recruitment shall be stopped after reaching the data saturation for different stakeholder groups. The mental health and public health experts shall be identified through the existing research and academic networks of the project PIs. Additional participants shall be identified using snowballing techniques with help of the recruited participants. The recruitment shall be stopped after reaching the data saturation for different stakeholder groups.

For feasibility and validity testing, a list of eligible and interested schools and colleges shall be prepared. The youth, their parents and teachers from these schools and colleges shall be requested to express their interest in participating in the validity testing. A random selection method using a computer-generated selection shall be used to pick a proportionate random sample to recruit students based on grade levels and gender representation from among the list of the eligible and interested schools and colleges at each site. A random selection method using a computer-generated selection shall be used to pick a proportionate random sample of parents and teachers.

The different phases of the study are summarised in **Table 1**.

**Table 1 T1:** Summary of the different phases of the study.

Phase	Participants	Methods	Output
Intervention development	Youth (children, adolescents, young adults), parents, teachers, experts	Literature review, FGDs, IDIs, NGT	Draft modular intervention package
Feasibility testing	Small sample (youth, parents, teachers)	Pilot delivery, qualitative and quantitative feedback	Refined intervention
Validation	Larger sample (youth, parents, teachers)	Pre-post assessments, process evaluation	Validation data

### Intervention development and validation process

2.6

The intervention will consist of a comprehensive package of prevention- focused interventions targeted at youth (children, adolescents, young adults), parents and teachers for excessive and problematic use of digital technology and mitigate the risk of associated stress, depression, anxiety, addiction among youth. The package of interventions shall be developed using a co-creation approach with various stakeholders including the youth, teachers, parents, and mental health professionals, public health experts, and program or policy experts using the six steps in quality intervention development (6SQuID) framework (66) and new framework for developing and evaluating complex interventions (67). These frameworks will guide problem definition, identification of modifiable factors, selection of change mechanisms, delivery strategies, testing, refinement, and evaluation.

#### Theoretical underpinnings

2.6.1

The intervention will be theoretically grounded in established psychological and behavioural frameworks, including the transtheoretical model of health behaviour change, social cognitive theory, theory of planned behaviour, self-determination theory, Knowles’ theory of adult learning, and the theory of reasoned action. These theories collectively inform the selection of cognitive, behavioural, and motivational strategies aimed at enhancing awareness, self-monitoring, decision-making, and sustained behaviour change. In addition, the strategies recommended in the previously published literature and as recommended by the stakeholders that are grounded in other theoretical constructs shall also be used.

The goals of the intervention are to promote responsible digital technology use, reduce risk factors for problematic use, enhance coping and self-regulation skills, foster healthy offline routines, and strengthen the role of parents and teachers as facilitators of digital well-being.

#### Procedure

2.6.2

The development and testing of the intervention shall be based on the six steps in quality intervention development (6SQuID) framework and the new framework for developing and evaluating complex interventions (23–25). These shall include Step 1- defining and understanding the problem and its causes; Step 2- clarifying which contextual factors are malleable and have greatest scope for change; Step 3- identifying how to bring about change: the change mechanism; Step 4- identifying how to deliver the change mechanisms; Step 5- testing and refining on small scale; Step 6- collecting sufficient evidence of effectiveness to justify rigorous evaluation/implementation.

#### Development of the intervention

2.6.3

The Steps 1–2 shall include a comprehensive analysis of the nature and extent of the problem and contributory factors. It shall be facilitated using desk review of existing literature and stakeholder participations. The existing research on the challenges encountered with the use of technology (e.g., impaired control over frequency, duration, and context of use) shall be searched. The review will also explore the contributory factors to these challenges. These would include psychological, behavioural, and environmental factors. This shall help identify key areas of focus for interventional components. Additionally, it will identify evidence-based interventional strategies that have been previously evaluated for their effectiveness in promoting responsible technology use and mitigating associated risks.

Stakeholder interviews will intend to understand the specific challenges and concerns related to digital technology use from the perspectives of key stakeholders. FGDs and IDIs will be conducted with each type of stakeholder to gather qualitative insights into their experiences, perceptions, and difficulties in managing technology use.

The qualitative findings from FGDs and IDIs will play a key role in the development of the intervention package. Thematic analysis will identify key challenges, behavioural patterns, contextual factors, and stakeholder priorities related to digital technology use. These themes will be mapped onto modifiable risk and protective factors. This will guide the identification of intervention targets and strategies.

Step 3 and 4 shall include identifying how to bring about change i.e. the change mechanism and identifying how to deliver the change mechanisms. An expert panel shall be constituted for finalization of the interventions for the package. This shall involve review of the information captured from the desk review and stakeholder interviews by a panel of the experts including psychiatrists, psychologists, technology experts, educationists, public health experts. The goal shall be to review the insights from the stakeholder interviews and existing literature to identify key strategies and interventions to be included in the package. A structured Nominal Group Technique (NGT) approach shall be used for this purpose.

A framework for intervention delivery shall be developed. The intervention package will comprise multiple, role-specific components for youth, parents, and teachers, developed through stakeholder consultations and expert consensus. This will involve systematically categorizing the interventions recommended by experts into a multi-tiered intervention delivery framework. The framework will be structured into four sets of intervention- youth set (children, adolescents, young adults), parental set, teacher set, collaborative set. The intervention package will be designed for practical implementation. This can be used on an as-needed basis. This will allow its integration into their daily routines effectively. The package shall be developed in a modular format. This will allow the use of different components on as- needed basis across diverse settings. The outcome will be a comprehensive, adaptable package of interventions.

#### Feasibility assessment

2.6.4

Step 5 shall include testing and refining intervention on a small scale. The feasibility assessment of the intervention shall be carried out using a quasi-experimental, mixed-methods approach. Participants will be briefed in advance that this phase constitutes a feasibility and formative feedback assessment of a newly developed intervention package. Each group will be offered the interventions designed specifically for them (youth, parents, and teachers).Participants will evaluate each intervention on a Likert scale for clarity, perceived effectiveness, usefulness, and practicality. Additionally, a semi-structured questionnaire will gather qualitative feedback regarding their experiences, challenges, and suggested improvements. Students, parents and teachers will provide separate feedback on the individual interventions. The outcome of this step will be a set of feedback and recommendations regarding required changes to the package of prevention- focused interventions. The findings will be documented and shared with the expert panel for review. The experts will deliberate upon the findings and recommend the modifications for the intervention package.

#### Intervention validation

2.6.5

Step 6 shall focus on collecting the validation data to justify rigorous evaluation/implementation.

The interventions shall be evaluated using a quasi-experimental, mixed-methods pre–post design. This shall be focused on validation, feasibility, and process outcomes. Base-line assessments shall be carried out using quantitative and qualitative measures. These shall include Structured proforma for socio- demographic details, Structured proforma for details of use of digital devices and internet, Smartphone Addiction Scale- Short Version (26), The Internet Addiction Test (IAT)- 6 item (27), Bergen Social Networking Addiction Scale (28), MULTICAGE CAD 4 (29), The Internet Gaming Disorder Scale-Short-Form (IGDS9-SF) (30), Gaming Disorder and Hazardous Gaming Scale (GDHGS) (31), Brief Biosocial Gambling Screen (BBGS) (32), Screen time Questionnaire. Participants from each group will receive the interventions designed specifically for them. young adults), parents, and teachers). The investigators on the project, project staff and other experts shall offer the intervention to the participants. Post- intervention assessments shall be carried out using quantitative and qualitative measures. These shall be guided by the Recommendations made in the new framework for developing and evaluating complex interventions and Moore’s framework for process evaluation.

Standard scoring procedures will be used for all instruments. Established cut-off scores will be used to classify the severity of problematic use (for example, SAS-SV and IAT-6). Other scales shall be interpreted using polythetic criteria and established scoring approaches consistent with prior validation studies (for example, BSNAS and IGDS9-SF). For scales where universally accepted cut-offs are not available, continuous scores will be analysed.

Various steps involved in the process have been summarised in **Figure 1**.

**Figure 1 f1:**
[figure not shown]
Various steps involved in the process based on the six steps in quality intervention development (6SQuID) framework.

Baseline assessments will be conducted immediately prior to the delivery of the intervention. Post-intervention assessments will be conducted immediately after completion of the intervention package. Long-term follow-up assessment is not planned in the present validation phase, as the focus is on feasibility, acceptability, and short-term proximal outcomes.

#### Outcome measures

2.6.7

Recommendations made in the new framework for developing and evaluating complex interventions and Moore’s framework for process evaluation shall be used to interpret outcome results by examining what happened during implementation, to explain variation in outcomes across settings or populations and to support replication, adaptation, and scaling of interventions.

Moore’s framework for process evaluation of complex interventions provides a structured approach to understanding whether an intervention works. Also, it helps understand how and why it produces change. The framework emphasizes mechanisms of impact (e.g., changes in knowledge, skills, competence), implementation processes (e.g., fidelity, reach, quality), contextual influences, and short- and long-term outcomes. The present study aims to validate a newly developed, multi-component prevention package. The mapping of outcomes to Moore’s domains allows systematic examination of mechanisms driving behaviour change, implementation feasibility, and contextual variability across sites. This approach is particularly relevant for complex, multi-stakeholder interventions implemented in real-world educational settings.

The primary outcomes shall be the perceived change in knowledge, skill and confidence levels, and improvement in decision-making. The secondary outcomes shall include satisfaction with the intervention package; feasibility and acceptability of the intervention package; perceived long-term impact. In addition, contextual and implementation variables such as participation, context, fidelity and quality, engagement and motivation, and unintended effects shall also be assessed.

A mapping of these outcome measures to specific domains has been presented in **Table 2**. The primary and secondary outcomes of the study were mapped to specific domains of Moore’s framework. This was done with an aim to ensure conceptual alignment between intervention mechanisms, implementation processes, and measurable outcomes. Knowledge, skills, and confidence were categorized under mechanisms of Impact. Decision-making and perceived long-term impact were mapped under outcomes. Feasibility, acceptability, satisfaction, and contextual variables were mapped to implementation.

**Table 2 T2:** Study outcomes/variables mapped to Moore’s domains.

Outcomes/Variables	Domain	Description
Primary outcomes		
Knowledge	Mechanisms of impact (Declarative Knowledge)	Understanding of healthy technology use, awareness of risks, knowledge of strategies
Skills	Mechanisms of impact (Procedural Knowledge)	Ability to apply strategies, feasibility of skills in real-life contexts
Confidence	Mechanisms of impact (Competence)	Self-efficacy and confidence in managing technology use
Decision-making	Outcomes	Changes in choices and self-regulation related to technology use
Secondary outcomes		
Satisfaction	Satisfaction	Overall satisfaction, perceived usefulness, willingness for future programs
Feasibility	Implementation plus context	Attendance feasibility, session length, applicability in real-life settings
Acceptability	Implementation plus satisfaction	Clarity, comfort, relevance, engagement
Perceived long-term impact	Outcomes	Sustainability, long-term benefit, likelihood of recommendation
Other variables		
Contextual and implementation variables	Participation (Reach/Dose)	Explains exposure and dosage effects
	Context	Explains variability across sites and populations
	Fidelity and quality	Distinguishes intervention vs implementation failure
	Engagement and motivation	Explains mechanisms driving behaviour change
	Unintended effects	Identifies unexpected positive/negative consequences

The assessments shall be carried out using quantitative and qualitative measures. These shall include structured questionnaires and FGDs and IDIs.

### Statistical analysis plan

2.7

The data shall be analysed using quantitative and qualitative data analysis techniques. Descriptive statistics will be used to summarise socio-demographic characteristics, baseline patterns of digital technology use, and outcome measures for youth, parents, and teachers. Continuous variables will be reported as means with standard deviations or medians with interquartile ranges, as appropriate. Categorical variables will be presented as frequencies and percentages.

The clustering of participants within sites will be accounted for in the analysis. Mixed-effects models will be used. The study site will be included as a random effect to account for intra-site correlation and between-site variability.

For the validation phase, pre–post comparisons will be conducted within each participant group. Changes in primary and secondary outcome measures will be assessed using paired t-tests (Cohen’s d for paired samples) for normally distributed continuous variables and Wilcoxon signed-rank tests (effect size r) for non-normally distributed variables. For categorical outcomes, McNemar’s test (odds ratios or appropriate measures of association) will be applied. Where outcome measures are collected using multiple scales across domains of digital technology use, composite scores will be analysed according to standard scoring guidelines. Subgroup analyses may be conducted by age group, gender, and site to explore variability in outcomes. Missing data patterns will be examined prior to analysis. Sensitivity analyses may be conducted where appropriate. All statistical tests will be two-tailed, with a significance level set at p < 0.05.

Qualitative data from FGD, IDIs, and open-ended feedback questionnaires will be analysed using thematic analysis. Transcripts will be coded independently by at least two researchers to enhance credibility. Codes will be grouped into themes reflecting feasibility, acceptability, clarity, engagement, contextual influences, and perceived impact of the intervention. Discrepancies in coding will be resolved through discussion. An audit trail will be maintained.

A convergent mixed-methods approach will be used for data integration. Quantitative and qualitative data will be analysed in parallel during the feasibility and validation phases. Integration will occur at the interpretation stage. A triangulation approach will be used to compare findings across data sources. Convergence, complementarity, or divergence between quantitative and qualitative findings will be systematically examined.

Intention-to-treat (ITT) analysis will be used for the primary analyses. All participants enrolled in the study will be included in the analysis. This will be done irrespective of their level of participation or completion of the intervention. Missing data patterns will be examined (e.g., missing completely at random, missing at random, or not at random). Appropriate imputation techniques will be used to handle missing data. Sensitivity analyses (including complete-case analysis and comparison with imputed datasets) will be done to assess the robustness of findings.

The primary outcomes will be analysed without adjustment, as these are predefined and limited in number. For secondary outcomes and multiple sub-scale analyses, appropriate adjustments for multiple comparisons will be considered to control the risk of Type I error.

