### Sample size

2.4

For intervention development: for focus group discussions (FGDs) and in-depth interviews (IDIs) recruitment will continue until data saturation is achieved for each stakeholder group. We anticipate conducting at least one FGD per stakeholder group per site, resulting in a minimum of 18 FGDs across six sites. Additional FGDs may be conducted if data saturation is not achieved. We anticipate conducting approximately 5–8 IDIs per stakeholder category across sites. Recruitment will continue until thematic saturation is achieved.

For feasibility testing: A minimum of five participants per group (i.e. youth, parents, and teachers) will be recruited from one school and one college at each site, resulting in a total sample of at least 30 participants. These participants will be different from the ones which were included in the sample for the development of the intervention package.

For validity testing: The minimum required sample size was calculated to detect a medium effect size of 0.5 with a two-sided alpha of 0.05 and a power of 95%. This resulted in a requirement of 53 participants per group. Accounting for an anticipated dropout rate of approximately 10%, at least 59 participants per group will be recruited. With three participant groups, the total planned sample size will be a minimum of 354.

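### The test and effect measure for each continuous primary outcome depend on the observed distribution, so what is estimated is not fixed in advance

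*Protocol article*

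**What the plan says.** All references are to the protocol article.

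- Section 2.7 (Statistical analysis plan) states that in the validation phase "pre–post comparisons will be conducted within each participant group". It continues: "Changes in primary and secondary outcome measures will be assessed using paired t-tests (Cohen’s d for paired samples"), and this applies "for normally distributed continuous variables and Wilcoxon signed-rank tests (effect size r) for non-normally distributed variables". The section names no normality test, threshold or distribution to be examined.
- Section 2.6.7 (Outcome measures) lists what the rule acts on: "The primary outcomes shall be the perceived change in knowledge, skill and confidence levels, and improvement in decision-making". With three participant groups, that gives 4 × 3 = 12 primary comparisons, if all four outcomes are scored as continuous.
- The paragraph before the rule in section 2.7 says: "Mixed-effects models will be used. The study site will be included as a random effect". It does not say whether this model or the paired tests are primary.
- Later in section 2.7, under intention-to-treat: "Appropriate imputation techniques will be used to handle missing data", with complete-case results compared against imputed data sets.
- Section 2.4 (Sample size) gives a number of participants "calculated to detect a medium effect size of 0.5", with 53 required per group and 59 after about 10% dropout.

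**The concern.** The two branches answer different questions. The paired t-test with d concerns the mean change. The signed-rank test with r concerns a rank-based shift. If the observed distribution chooses between them, the estimand of a primary outcome is not fixed before the data are seen.

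Four consequences follow:

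1. Knowledge, for example, could be reported as d in youth and as r in teachers, leaving no common scale on which to read the package's three components.
2. A result given as r cannot be read against the standardised effect on which the study was sized.
3. The mixed-effects model promised for site clustering estimates mean changes, so the signed-rank branch has no counterpart in it.
4. If several imputed data sets are created, mean change and its standard error combine by Rubin's rules. The signed-rank test with r has no equally standard route and would need its own stated method.

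Separately, the normality that matters for a paired t-test is that of the paired differences, and the sentence does not say so.

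**Working it through.** **Step 1: which analysis the sample size belongs to.** Inputs from section 2.4: d = 0.5, two-sided alpha 0.05, power 95%.

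- Normal approximation for paired data: n = ((1.960 + 1.645)/0.5)² = 51.98, so 52.
- Exact noncentral t: 53.94, so 54. Power at n = 53 is 94.7%.
- Two independent means would need 104 per group.
- Dropout: 53/0.90 = 58.9, so 59.

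The stated 53 and 59 are reproduced within rounding, and 53 is a paired t-test figure. For the same d = 0.5, the signed-rank test would need 53.94/(3/π) = 56.5, so 57, if the differences are normal. At its worst-case efficiency of 0.864 it would need 53.94/0.864 = 62.4, so 63.

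**Step 2: r against the planned 0.5.** Take r = Z/√n, with n the number of pairs and normal differences. In large samples r ≈ √3 × (Φ(√2 × d) − 0.5).

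- d = 0.5: Φ(0.707) = 0.760, so r ≈ 1.732 × 0.260 = 0.45.
- d = 0.8: Φ(1.131) = 0.871, so r ≈ 1.732 × 0.371 = 0.64.

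Simulation at n = 53 gave the same values, 0.45 and 0.64. A group that met the planning effect exactly would show an r of about 0.45 and could be misread as falling short.

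**Step 3: effect on error rates.** 3,000 simulated data sets per row, 53 pairs, tests at the 5% level (Monte Carlo error for a 5% rate: √(0.05 × 0.95/3000) = 0.4 points). The distributions are assumptions, because the article gives no scale ranges or SDs for the primary outcomes.

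| Assumed data | Type I error, t | Type I error, Wilcoxon | Verdicts differ, no change | Verdicts differ, true change |
|---|---|---|---|---|
| Skewed baseline, normal differences | 0.048 | 0.045 | 2.0% | 5.8% |
| All normal | 0.051 | 0.050 | 1.8% | 5.6% |
| Single 1–5 item | 0.052 | 0.049 | 0.9% | 2.2% |

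The switching procedure itself was not simulated, but it can be bounded. Whatever rule picks the test, it rejects only if at least one of the two does, and P(either rejects) = (t + Wilcoxon + differ)/2.

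- Skewed baseline: (0.048 + 0.045 + 0.020)/2 = 0.057.
- All normal: (0.051 + 0.050 + 0.018)/2 = 0.060.
- Single item: (0.052 + 0.049 + 0.009)/2 = 0.055.

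In these scenarios the switch cannot raise type I error above about 6%.

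**Step 4: whether the object of the check matters.** Same simulations, with Shapiro-Wilk at 5% as an assumed rule. With a skewed baseline and normal differences, checking the pre and post scores picks Wilcoxon in about 99% of data sets. Checking the differences picks the t-test in about 95%. The two checks disagree in about 94%. With all-normal data they disagree in about 13%. With a single 1–5 item both always pick Wilcoxon. The branch can thus hinge on a point the sentence leaves open.

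**Step 5: mixing across groups.** If each group independently takes the Wilcoxon branch with probability p, the three groups do not all share one test with probability 1 − p³ − (1 − p)³. A further simulation (mean of four 5-point items, latent correlation 0.5, moderate baseline) had the differences failing normality in 10% to 12% of samples:

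- p = 0.10: 1 − 0.001 − 0.729 = 0.27.
- p = 0.12: 1 − 0.002 − 0.681 = 0.32.

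So even when the differences are what is checked, tests could be mixed for a given outcome in roughly a quarter to a third of studies under these assumptions. If p is close to 0 or 1, mixing almost disappears.

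**The case against.** The case for leaving the text alone has real force.

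- A reader might infer that normality will be checked on the wrong distribution. The article does not support that. It describes no check, and the sentence opens by speaking of changes in the outcomes, while section 2.6.7 words the primary outcomes partly as perceived change. The change score is a possible reading, and how it is examined is detail that a fuller plan may hold. Only the ambiguity stands.
- A reader might infer that false positives are inflated. The working does not show that. Each test alone stays near 5%, the bound for any switch is about 6%, and the verdicts seldom differ.
- A reader might infer that the signed-rank branch cannot be combined over imputations. That is too strong. The article does not name multiple imputation, though its plural reference to imputed data sets suggests it, and a rank-based shift with a bootstrap standard error could be combined. It would need a stated method.
- Mixing across groups may not happen. If ratings are high at baseline, or each outcome is a single item, nearly every group may take the same branch.
- The three groups are analysed separately, and the article disclaims establishing causal effectiveness at this stage.

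What survives is that the switch is a stated rule, not an omission, and it expressly covers the primary outcomes. A later analysis plan could remove it only by departing from this sentence. The promised mixed model does not resolve the matter, because the section never says which analysis is primary.

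**Conclusion.** The point holds in a limited form. The estimand and effect measure of up to 12 primary comparisons are left to the observed distribution. They can differ between youth, parents and teachers, leave the scale of the planned effect when r is reported, and do not line up with the mixed model in the same section. The wording on variables is ambiguous, not an error.

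The cost lies in interpretation and comparability, not in the validity of the tests. The error-rate and mixing figures rest on assumed distributions and an assumed normality test. The mixing figures also assume equal and independent probabilities in the three groups. The conclusion that the estimand is not fixed needs none of these assumptions. This is a worthwhile, inexpensive correction and does not threaten the study.

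**What to change.** In section 2.7, delete the normality switch for continuous primary outcomes and name one primary analysis for every such outcome and group:

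- mean pre-post change with a 95% CI from the mixed-effects model already planned, with site as a random effect, set up so that each participant's pre-post pairing is kept (for example with the paired difference as the response);
- Cohen's d for paired samples in all groups and outcomes, so that results can be read against the planned 0.5;
- if multiple imputation is used, estimates combined by Rubin's rules;
- the Wilcoxon signed-rank test kept as a sensitivity analysis;
- if a distribution is inspected at all, that of the paired differences or model residuals, and only to inform interpretation.

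The cost is wording only, and section 3 states that data collection has not begun. The downside is slightly less power than the rank test if the differences are very skewed. In that case the sensitivity analysis will still show the rank result.
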